### Intervention Overview

#### Intervention Format

This study consists of a self-administered video-based stigma reduction app using an RCT design among Black adults (ages 18-45 years) from diverse ethnic backgrounds with moderate to severe depression and/or anxiety (9-item Patient Health Questionnaire ³10 or 7-item generalized anxiety disorder ³10) who have not accessed mental health services in the past year.

The intervention videos involve 6- to 12-minute videos, offering narratives on treatment and recovery by people living with mental illness from diverse backgrounds including narratives of depression illness and recovery [58,59]. In the adapted (concordant) intervention arm, participants will be offered video content from someone with the same or similar sociodemographic background based on their reported characteristics at screening [60]. The standard (discordant) intervention arm will involve video content from someone from a different sociodemographic background. The 2 intervention conditions will be delivered on a secure HIPAA (Health Insurance Portability and Accountability Act)-compliant platform. Content will be available in English at an eighth-grade reading level [61,62]. New sessions will be prompted each week based on the experimental condition arm, and usage data will be collected. The study will include individuals from various age groups, education and income levels, and gender identities. Study participants will be randomly assigned to 1 of 3 arms: a standard video-based app (n=30), a video-based app modified with a concordant individual (n=30), and a waitlist control (n=30).

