#### Data Analysis and Power Calculation

As a feasibility study, we will pilot the outcome analyses (to detect a signal and estimate direction of analysis), recognizing that the trial may be underpowered. On the basis of the sample size of 90 (n=30 in each treated group and control group) and power at 72%, we will be able to detect a medium effect size of Cohen *d*=0.49 at α=.05 comparing the intervention versus control proportions for any engagement in mental health care services.

For the continuous outcomes (such as Group-Based Medical Mistrust Scale), we will use generalized linear mixed models with a gamma distribution for continuous outcomes. If variables are not normally distributed, we will explore a transformation. For binary outcomes, we will use Poisson or negative binomial regression depending on the variance.

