### Randomization and Blinding

#### Randomization Scheme

Participants will be randomized to 1 of 3 arms: a standard video contact arm, a concordant video contact arm, and a waitlist control arm as outlined in our CONSORT diagram (Figure 1). Assignment to the 3 arms in a 1:1:1 allocation ratio will be determined centrally by the principal investigator according to a computer-generated random schedule (ie, in Stata [StataCorp]). There is no practical way to fully blind the study participants to treatment assignment versus waitlist and accomplish the objectives of the study. To avoid bias among participants receiving the concordant or standard video assignment, we will conceal treatment arm allocation. We are testing the salience of concordance across sociodemographic characteristics; unblinding would prevent unbiased testing of the role of concordance. The study participants will be blinded to the two intervention arms and will be unaware which intervention arm they were assigned throughout the study. The research study staff and biostatistician (who will be conducting the outcome assessments and analysis, respectively) will be blinded to treatment assignment status. The participants assigned to the waitlist will receive access to the concordant video contact intervention after they have completed their 12-month study assessment. To avert chance imbalances by ethnicity and sex, we will stratify randomization by ethnicity (African American, Afro-Caribbean or Afro-Latino, and African immigrant) and sex. The regression models for the primary analysis include the stratification variables as covariates to ensure the estimated standard errors are accurate. We hypothesize that the concordant video arm will be superior to the standard video arm. The standard video arm is needed to test our hypothesis and understand the mechanistic effect of each therapeutic target.

Reliability and validity data for the study assessments are shown in Table 2 [65-68].

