### Study Outcomes

Our study will assess our ability to recruit and retain study participants and measure usability, satisfaction, and adherence. The primary outcome will be mental health service use, assessed 4 weeks after the intervention and at 3 months after the booster sessions and again at 6 and 12 months, following booster sessions. Secondary outcomes will include anticipated, enacted, and internalized stigma; medical mistrust; and help-seeking behavior. The primary outcome is defined as any engagement with mental health services: this includes intake appointments, follow-up appointments, or scheduled appointments for mental health with a psychiatrist, physician or clinician, clinical psychologist, therapist, or self-report mental health service use (verified by electronic health records). At baseline, participants sign a release of information (ROI) form to allow the study team to obtain their medical records from their designated health system. The ROI form expires at 6 months, and a new ROI will be obtained to ensure the study team is able to retrospectively review use of mental health services at study completion at 12 months.

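### The rule for binary outcomes, Poisson or negative binomial regression chosen by the variance, is a count-data rule that cannot work for the yes/no primary outcome

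*Protocol article*

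**What the plan says.** Data Analysis and Power Calculation gives one sentence on the model for yes/no endpoints: "For binary outcomes, we will use Poisson or negative binomial regression depending on the variance".

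Study Outcomes makes this the sentence that governs the primary analysis: "The primary outcome is defined as any engagement with mental health services". The power statement treats that outcome as a proportion too, "comparing the intervention versus control proportions for any engagement in mental health care services", with a stated power of 72%, and says that "we will be able to detect a medium effect size of Cohen *d*=0.49 at α=.05".

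The only remark about the accuracy of standard errors is in Randomization Scheme: "The regression models for the primary analysis include the stratification variables as covariates to ensure the estimated standard errors are accurate". The article names no robust variance, log-binomial model or logistic model. It gives no event rates, does not say whether the test is one- or two-sided, and does not say whether the two video arms are pooled against the waitlist.

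**The concern.** Choosing between Poisson and negative binomial regression by looking at the variance is the standard check for overdispersion in counts, such as number of visits. The primary outcome is not a count. Each participant contributes a 0 or a 1, and such data are always less variable than a Poisson variable with the same mean. The rule therefore has no valid trigger, and one of its two named models never applies.

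The other model, Poisson, is sound for a risk ratio only if its variance is corrected. With its own variance it takes p where the truth is p(1-p), so standard errors are too large, confidence intervals too wide and p-values too big. At stake is the preliminary efficacy estimate that this pilot is meant to hand to a fully powered trial.

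**Working it through.** **Inputs from the article.** 30 participants per arm, allocated 1:1:1; effect size 0.49; α = 0.05; binary primary outcome.

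**Assumptions, because the article is silent.** Control engagement rate p0 from 0.10 to 0.60. The intervention rate p1 is set so that Cohen h = 0.49, reading the stated effect as the proportion version of Cohen's measure. The main case pools the video arms (60 v 30) and tests two-sided; alternatives follow. Dropout is not applied.

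**The plan's own figure.** Normal approximation, power = Φ(0.49/√(1/n0 + 1/n1) − z).
- 60 v 30: 0.49/√(1/30 + 1/60) = 2.191. One-sided, Φ(2.191 − 1.645) = 70.8%. Two-sided, Φ(2.191 − 1.960) is about 59%.
- 30 v 30: 0.49/√(2/30) = 1.898. One-sided 60.0%, two-sided 47.5%.

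Of these, only the one-sided pooled comparison comes within 2 points of the stated 72%. One-sided results are therefore shown below as well.

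**Why the rule has no trigger.** For a 0/1 outcome the ratio of variance to mean is p(1-p)/p = 1 − p, which is below 1 for any p above 0. In three illustrative 60 v 30 datasets the Pearson dispersion of the Poisson fit was 0.73, 0.57 and 0.32. The negative binomial likelihood was highest as its dispersion parameter went to 0, which is the Poisson model. Any positive dispersion enlarged the standard error further.

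**Inflation of the standard error of the log risk ratio.**
- Poisson, model-based: √(1/(n0·p0) + 1/(n1·p1)).
- Binomial, which a robust variance targets: √((1−p0)/(n0·p0) + (1−p1)/(n1·p1)).

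Example, p0 = 0.30, p1 = 0.539, 60 v 30. Poisson variance: 1/9 + 1/32.34 = 0.1420. Binomial variance: 0.70/9 + 0.461/32.34 = 0.0920. The standard-error ratio is √(0.1420/0.0920) = 1.24.

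**Power.** Exact enumeration of two binomials, Wald test on the log risk ratio, no covariates, samples with a zero cell counted as non-rejection. The power columns are for 60 v 30, two-sided:

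| p0 | p1 | SE ratio | Power, model-based | Power, robust | Relative loss, two-sided | Relative loss, one-sided |
|---|---|---|---|---|---|---|
| 0.10 | 0.288 | 1.07 | 25.5% | 35.4% | 28% | 10% |
| 0.20 | 0.424 | 1.15 | 31.8% | 48.2% | 34% | 21% |
| 0.30 | 0.539 | 1.24 | 27.7% | 49.9% | 44% | 32% |
| 0.40 | 0.642 | 1.36 | 20.8% | 50.7% | 59% | 43% |
| 0.50 | 0.735 | 1.51 | 13.1% | 50.3% | 74% | 58% |
| 0.60 | 0.819 | 1.71 | 6.1% | 50.0% | 88% | 74% |

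For 30 v 30, two-sided, the standard-error ratio runs from 1.08 to 1.80, and the relative loss is 52% at p0 = 0.30 and 68% at 0.40. At low rates small cells affect the exact Wald results; the normal approximation for 60 v 30, two-sided, gives a loss of 12% at 0.10 and 24% at 0.20.

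**Type I error (nominal 5%, two-sided, 60 v 30).** Model-based Poisson gives about 1.5% at a common rate of 0.30 and 0.5% at 0.50. With robust errors the figures are 4.2% and 4.6%.

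**Do the stratification covariates help?** In a simulation of 2,000 trials per scenario, adjusted for ethnicity (three levels) and sex, 60 v 30, type I error at 0.30 was 1.4% with model-based Poisson, 4.4% with robust Poisson and 4.8% with logistic regression. Power at 0.30 v 0.537 was 26.6%, 50.0% and 58.0%. These are close to the unadjusted results, so covariates do not cure the problem.

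**The case against.** The strongest reply is that Poisson regression with a robust variance is an accepted way to estimate a risk ratio, and that a condensed article may leave the variance estimator to the full plan. That stands as far as it goes: the inflation and the power loss are conditional on model-based errors, and silence about robust errors does not show that they will not be used. It does not rescue the sentence. A robust variance needs no choice between Poisson and negative binomial driven by the variance, and the article's one statement on accurate standard errors relies on covariates, which do not correct a wrong variance function.

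A reader might infer that the plan throws away half or more of the power. The article does not support that as a general statement. It gives no event rates, and it enrols people "who have not accessed mental health services in the past year", so control rates of 0.10 to 0.20 are plausible; there the relative loss is about a tenth to a third, depending on sidedness.

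A reader might also infer a biased effect or false positives. Neither follows. The log link still targets the risk ratio, and the error is conservative. The article also concedes that the trial may be underpowered, and its feasibility criteria do not depend on this model. These points limit the consequence; they do not make the rule workable.

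Finally, the sentence may have been meant for counts of visits. The article names no such outcome, and on that reading the primary outcome would have no stated model.

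**Conclusion.** Wrong as written. That the selection rule cannot function for a yes/no outcome, and that negative binomial never applies, holds at every event rate and needs no assumption.

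The size of the harm is conditional. If model-based errors are used, for 60 v 30 and h = 0.49, standard errors are about 7% to 70% too large over control rates of 0.10 to 0.60. Two-sided power losses pass one half somewhere between control rates of 0.30 and 0.40, and one-sided losses between 0.40 and 0.50. If robust errors are used, this harm disappears and only the faulty rule remains. In a pilot that already concedes low power, the consequence is intervals that are too wide and a signal more easily missed.

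**What to change.** Replace the sentence on binary outcomes with: *Any engagement (yes/no) will be analysed by Poisson regression with robust (sandwich) standard errors, or by logistic regression with marginal standardisation to a risk ratio and risk difference, adjusted for the stratification variables.* Choose one of the two before the data are analysed. Drop negative binomial for binary outcomes, and keep the Poisson or negative binomial choice only for any analysis of visit counts.

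The cost is one sentence, with no new data. The article reports 75 of 90 participants recruited at submission and results due in March 2027, so the change can be made before the analysis.

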### Randomization and Blinding

#### Randomization Scheme

Participants will be randomized to 1 of 3 arms: a standard video contact arm, a concordant video contact arm, and a waitlist control arm as outlined in our CONSORT diagram (Figure 1). Assignment to the 3 arms in a 1:1:1 allocation ratio will be determined centrally by the principal investigator according to a computer-generated random schedule (ie, in Stata [StataCorp]). There is no practical way to fully blind the study participants to treatment assignment versus waitlist and accomplish the objectives of the study. To avoid bias among participants receiving the concordant or standard video assignment, we will conceal treatment arm allocation. We are testing the salience of concordance across sociodemographic characteristics; unblinding would prevent unbiased testing of the role of concordance. The study participants will be blinded to the two intervention arms and will be unaware which intervention arm they were assigned throughout the study. The research study staff and biostatistician (who will be conducting the outcome assessments and analysis, respectively) will be blinded to treatment assignment status. The participants assigned to the waitlist will receive access to the concordant video contact intervention after they have completed their 12-month study assessment. To avert chance imbalances by ethnicity and sex, we will stratify randomization by ethnicity (African American, Afro-Caribbean or Afro-Latino, and African immigrant) and sex. The regression models for the primary analysis include the stratification variables as covariates to ensure the estimated standard errors are accurate. We hypothesize that the concordant video arm will be superior to the standard video arm. The standard video arm is needed to test our hypothesis and understand the mechanistic effect of each therapeutic target.

Reliability and validity data for the study assessments are shown in Table 2 [65-68].

**Figure 1 figure1:**
[figure not shown]
CONSORT (Consolidated Standards of Reporting Trails) diagram.

**Table 2 table2:** Reliability and validity data for the study assessments.

Variables	Reliability and validity	Estimated administration time
4-item Reported and Intended Behavior Scale (Evans-Lacko et al [66], 2011)	Reliability: overall test-retest reliability was 0.75, and internal consistency, based on Cronbach α among items 5-8, was 0.85.	2 minutes
29-item Internalized Stigma of Mental Illness (Boyd et al [65], 2014)	Reliability: the original ISMIa reported test-retest reliability of 0.92	4-6 minutes
12-item Group-Based Medical Mistrust Scale (Shelton et al [67], 2010)	Reliability: Cronbach α for the full measure in previous studies (α=0.87-0.88). Validity: the total GBMMSb score and its 3 subscales were positively correlated with avoidance of health care (total score: *P*<.001; r=0.344).	3-5 minutes
20-item General Help-Seeking Questionnaire (Ibrahim et al [68], 2019)	Reliability: Cronbach α for the full measure in previous studies (α=0.91). Validity: the perceived quality of previous mental health care was positively related to intentions to seek help from a mental health professional for personal and emotional problems (rs55=0.51, *P*<.001) and suicidal thoughts (rs54=0.57, *P*<.001).	3-5 minutes

^a^ISMI: Internalized Stigma of Mental Illness.

^b^GBMMS: Group-Based Medical Mistrust Scale.

#### Missing Data

Data missing at follow-up could bias study findings. We plan to record the reason for dropout. When dropout occurs completely at random, the statistical analyses stated will provide appropriate statistical inferences. The multiple imputation approach will be conducted for follow-up data that are missing at random.

#### Planned and Interim Analysis

We hypothesize that the contact-based intervention arm that incorporates an approach using concordance will reduce stigma and lower medical mistrust, improving engagement in mental health services. Feasibility will be assessed by meeting our recruitment goals (90 participants), obtaining 80% of follow-up self-report data, and having a dropout rate of <20% in one or more treatment conditions, which is in line with previous mobile mental health intervention RCTs [69] and which would indicate the treatment format for future research. Recruitment and retention rates, acceptability, adherence to study, and treatment will be reported as percentages. The average USE and SUS scores will be reported.

We will assess the moderating role of sociodemographic factors (religiosity, migrant status, and socioeconomic status) by controlling for these variables in our pre-post assessments.

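### Moderation by religiosity, migrant status and socioeconomic status is to be assessed by covariate adjustment, which cannot show whether the arm effect differs across their levels

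*Protocol article*

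**What the plan says.** The only statement on moderation in the protocol article is in Planned and Interim Analysis: "We will assess the moderating role of sociodemographic factors (religiosity, migrant status, and socioeconomic status) by controlling for these variables in our pre-post assessments". It names both a question (moderation) and a method (adjustment).

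The other analysis statements are:
- Data Analysis and Power Calculation, continuous outcomes: "we will use generalized linear mixed models with a gamma distribution for continuous outcomes".
- The same section, binary outcomes: "For binary outcomes, we will use Poisson or negative binomial regression depending on the variance".
- Randomization Scheme: "The regression models for the primary analysis include the stratification variables as covariates to ensure the estimated standard errors are accurate". The stratification variables are ethnicity and sex.
- Expected Findings (Discussion): causal mediation analysis, with stigma and medical mistrust as possible mediators.

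None of these mentions an interaction between arm and a background factor, effect modification, or arm effects within subgroups.

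**The concern.** A model that contains arm and a covariate, but not their product, holds the arm effect equal at every level of the covariate. Its covariate coefficient says who scores higher or lower whatever the arm. Its arm coefficient is one effect, taken as common to everyone. Neither speaks to whether the app works better for, say, more religious participants or for migrants.

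This is more than a detail left to an unseen analysis plan, because the article commits to a procedure that does not match its question. A fuller plan that specified interactions would conflict with this sentence, and the sentence would still need correcting.

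At stake is what is carried forward. The Conclusions say that this trial is to inform a refined intervention and a fully powered trial. A statement that a background factor does or does not moderate the effect could shape that design, and the stated method gives no basis for one.

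**Working it through.** **1. What each model can estimate.** Let T be arm, M a moderator and Y an outcome score.
- Adjusted model: E(Y) = a + bT + cM. The arm effect is b at every level of M.
- Interaction model: E(Y) = a + bT + cM + dTM. The arm effect is b + dM, and moderation is d.

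The adjusted model contains no d. The same holds for the planned gamma and Poisson or negative binomial models, on the scale of their link.

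**2. Inputs.** From Data Analysis and Power Calculation: N = 90, 30 per arm, d = 0.49, α = .05. Assumed for illustration: linear model, SD 1, a single outcome score without baseline adjustment, a binary moderator split 50/50, and the two app arms pooled (60) against waitlist (30) unless stated.

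**3. The plan's own power figure.** The article says "we will be able to detect a medium effect size of Cohen *d*=0.49 at α=.05 comparing the intervention versus control proportions", with 72% power.
- SE of the arm effect = √(1/60 + 1/30) = √0.05 = 0.224, and 0.49/0.224 = 2.19.
- One-sided: Φ(2.19 − 1.645) = 70.8%, close to the stated figure.
- Two-sided: Φ(2.19 − 1.96) = 59.2%.
- 30 against 30: 60.0% one-sided, 47.5% two-sided.

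This sets the scale only. The moderation point does not depend on it.

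**4. Simulation of the two models** (4,000 runs per scenario, arm effect 0.49 SD averaged over the two levels).
- *Prognostic factor, no moderation* (covariate effect 0.8 SD, d = 0): the covariate is significant in 96% of runs. The interaction test rejects in 4.8%, its nominal rate.
- *True moderation, no marginal covariate effect* (d = 0.98, so arm effects of 0.49 − 0.49 = 0 and 0.49 + 0.49 = 0.98 SD at the two levels): the covariate is significant in 4.4% of runs, which is chance, and the adjusted arm effect averages 0.49. The interaction model estimates d at 0.975 on average and rejects in 57.6%.

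The adjusted model looks the same whether the effect is 0.49 SD for everyone or nil for half and 0.98 SD for the other half.

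**5. What the interaction can deliver.**
- Pooled, 60 against 30: variance of d = 1/30 + 1/30 + 1/15 + 1/15 = 0.20, SE = 0.447. The ratio to the main-effect SE is √(0.20/0.05) = 2.0.
- 95% half-width = 1.96 × 0.447 = 0.88 SD.
- Detectable at 80% power, two-sided = (1.96 + 0.84) × 0.447 = 1.25 SD.
- Power for d = 0.49: Φ(0.49/0.447 − 1.96) = 19%. For d = 0.98: 59%.
- One arm against another, 30 against 30: variance = 4/15, SE = 0.516, detectable = 2.80 × 0.516 = 1.45 SD. Power for d = 0.49 is 16%.

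**6. Effect of adjusting for baseline.** If the correlation between baseline and follow-up were 0.75 (an assumption, equal to the test-retest value in Table 2 for the Reported and Intended Behavior Scale), SEs shrink by √(1 − 0.75²) = 0.66. The pooled half-width becomes 0.88 × 0.66 = 0.58 SD and the detectable interaction 1.25 × 0.66 = 0.83 SD.

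**The case against.** The strongest reply is that this is one sentence about a side question in a pilot. Moderation by these factors appears in neither the objectives nor the hypotheses, and not among the outcomes. The article describes its outcome analyses as piloting, "recognizing that the trial may be underpowered", and its Limitations section says that the sample cannot settle effectiveness. All of that stands, and it limits how serious the point is.

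It may also be said that controlling for is loose wording for fitting interactions. Nothing in the article supports that. Where covariates are mentioned elsewhere, in Randomization Scheme, they are there for ordinary adjustment.

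Three stronger readings are tempting, but the documents do not support them:
- *That the analysis drops the randomized comparison because it refers to pre-post assessments.* The sentence does not say that arm is left out. Stigma and mistrust are measured at baseline and repeatedly afterwards, and the hypotheses compare arms, so the phrase may simply mean those repeated measures.
- *That the trial will report false moderators.* No rule says that a covariate coefficient will be read as moderation. Adjusted arm effects alone would fit the sentence equally well and would leave the question open. The simulation shows what follows if the coefficient is misread, not that it will be.
- *That the test of concordance is compromised.* Concordance is tested by the randomized concordant-versus-standard contrast, which does not rely on this sentence. Whether religiosity, migrant status or socioeconomic status modifies the effect is a different question.

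The figures in SD units are also only loosely tied to this trial. They do not apply to the primary outcome, which is binary, and baseline adjustment would narrow them.

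**Conclusion.** The point holds in a limited form. The stated method cannot answer the stated moderator question, and no other section of the article repairs it. This conclusion is a matter of model structure and does not depend on the numerical assumptions.

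The consequence is confined to an ancillary analysis, so it is a correction that should be made rather than one on which the trial's validity turns.

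The sizes above illustrate precision under the listed assumptions and are not forecasts for this trial. They show that even the right analysis can only be exploratory: at 60 against 30, an interaction as large as the planned main effect of 0.49 SD would be detected about one time in five.

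**What to change.** Replace the sentence with wording such as: *Moderation by religiosity, migrant status and socioeconomic status will be explored by adding arm-by-moderator interaction terms, one moderator at a time, to the between-arm outcome models. Interaction estimates and arm effects by level will be reported with 95% confidence intervals and regarded as exploratory.* If these variables are also wanted as adjustment covariates, say so in a separate sentence.

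Costs:
- With three arms, each binary or single-score moderator needs at least two interaction terms. Three moderators therefore need at least 3 × 2 = 6 per outcome, and more if a moderator has several categories.
- The intervals will be visibly wide, and with several moderators and outcomes some will exclude no interaction by chance. The exploratory label has to be kept in reporting.
- Table 1 lists a baseline demographic survey but does not itemize religiosity or socioeconomic status. The sponsor should confirm that all three factors are recorded at baseline in usable form.

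The Study Status section under Results places publication of results in March 2027. The wording should be settled before outcome data are analyzed by arm.
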